#### 12.6. Adjustment for multiple testing

No adjustment for multiple testing will be performed. Therefore, all outcomes rather than primary outcome will be considered hypothesis generation and p-value will not be reported.

#### 12.7. Confidence intervals, p-value and reporting conventions

Statistical significance level for primary outcome will be at the 0.05 level ( $\alpha = 0.05$ ). 95% confidence intervals for all study outcomes, as well as for all subgroup and sensitivity

analysis will be reported. P-value values  $\geq 0.001$  will be reported to 3 decimal places; values  $< 0.001$  will be reported as “ $< 0.001$ ”. Mean and SD values will be reported using one decimal place greater than the original data. Median and quantiles will use the same number of decimal places as the original data. Subjects who attend to baseline evaluation and final evaluation visits will be considered trial completers.

## 12.8. Adherence to the intervention

As a pragmatic trial aimed to evaluate the intervention effectiveness in a setting closer to a real-world scenario, the evaluation of outcomes will not consider patients adherence to the proposed intervention, maintaining the integrity of the intention-to-treat analysis.

## 12.9. Statistical software

The statistical software RStudio (version 4.3.1 or above) and IBM® SPSS Statistics (version 27.0.1 or above) will be used for all the analyses

## 13. Adverse event monitoring

No adverse events are expected to occur as a result of the intervention. However, there is potential for participants to experience stress related to the intervention, which will be recorded as part of the primary outcome of the study. Furthermore, given that the study involves blood collection, there is a possibility of harm not directly linked to the intervention. Anticipated adverse effects such as hematoma and local pain will be monitored. Any serious adverse effects beyond these will be recorded and reported, although such occurrences are considered highly unlikely. Additionally, during the follow-up phone calls, participants will be asked about their well-being and if they have experienced any changes or symptoms since the start of the study. This information will be documented to ensure the ongoing safety and monitoring of the participants, even though specific adverse event classification will not be applicable in this study.

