## 6. Trial interventions

### 6.1. Intervention group (Alexa's group)

Individuals assigned to the intervention group will receive the Smart Speaker EchoDot 3rd Gen (Amazon Echo®) device (i.e., Alexa) for home use, installed during a home visit following the baseline evaluation. The device will be programmed using a standard model developed by the research team, applied to each patient. The proposed model involves automatic interactions between the device and the patient, comprising:

1. Medication reminders: The device will be programmed to automatically issue reminders at specified times for patients to take their medications and insulin, following the medical prescription provided by the attending physician.
2. Glucose test reminders: Automatic reminders for glucose testing will also be programmed, aligning with each patient's individual testing frequency and routine.
3. Educational health tips: At two pre-defined times during the day, set in consultation with the patient during installation, the device will emit a sound alert and deliver daily flash briefings centered on health education messages. These briefings will include a greeting message, three messages related to health education, and a farewell message. The health education-related messages

comprise a total of 42 unique messages developed by the research team, divided into two groups:

- a. 28 messages that will be repeated every 4 weeks, one message each day, so that each message will be played three times over the 12-week study period. A detailed version of the phrases is available in Table 1 (English, translated) and Appendix B (original version in Brazilian Portuguese).
  - b. 14 messages divided into 7 sets of 2 messages that will be repeated every week, two messages each day, so that each message will be played 12 times throughout the study. A detailed version of the phrases is available in Table 2 (English, translated) and Appendix C (original version in Brazilian Portuguese).

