| 19 | Whenever you check your blood glucose level or have a hypoglycemia episode, write it down in a notebook with the date and value.                                                                        |
| 20 | If you have a hypoglycemia episode, remember that just a tablespoon of sugar is enough to reverse it. Be careful, as excess sugar can also be a problem.                                                |
| 21 | Have an emergency plan for hypoglycemia, and remember to take something to eat when you leave home.                                                                                                     |
| 22 | Maintain an adequate stock of diabetes-related medications and supplies, such as glucose test strips, medications, and insulin needles, to avoid interruptions in your treatment.                       |
| 23 | How about learning relaxation techniques like deep breathing and meditation to cope with stress? I can help you with that; just ask, "Alexa, open the meditation skill."                                |
| 24 | Sometimes, it's normal to feel that having diabetes is a burden, and these emotions are part of the process of learning to cope with the disease. Pay attention to your mental and emotional health.    |
| 25 | Diabetes is a manageable condition; with proper treatment, you can keep your blood glucose levels in check and lead a good and normal life.                                                             |
| 26 | Seek support from family, friends, and support groups to share experiences, tips, and challenges related to diabetes treatment. Having people who understand and support you can make a big difference. |
| 27 | The goal of diabetes treatment is to improve your quality of life and overall well-being. Focus on taking care of yourself and making healthy choices that bring long-term benefits to your life.       |

|    |                                                                                                           |
|----|-----------------------------------------------------------------------------------------------------------|
| 28 | Even with a diabetes diagnosis, you don't have to give up all the things you love or the foods you enjoy. |
|----|-----------------------------------------------------------------------------------------------------------|

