### 6.3. Follow up phone calls

Follow-up of participants will be maintained through five follow-up phone calls, conducted every two weeks. Additionally, participants from the control group will receive an extra phone call, equivalent to the device installation, to ensure equivalent contact in both groups. A detailed timeline for these calls is provided in the following sections. The purpose of the follow-up phone calls is to ensure ongoing monitoring, and no behavioral or motivational interventions will be conducted during them.

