## 9.1. Data collected

**Identification data:** Full name, medical record number, phone number, address, and email address.

**Clinical interview and baseline evaluation:** Sociodemographic information, comorbidities and personal medical history, daily schedule, mini-mental state examination (MMSE) score,

up and go test, sit-to-stand test, usual gait speed test, height, hip and calf circumference, Katz activities of daily living index score, and Lawton instrumental activities of daily living scale

**Clinical evaluation:** Blood pressure (three repeated measures), handgrip strength (three repeated measures in the non-dominant arm), body weight, and score on the Brazilian version of the following:

- SRQ-20
- SF-36
- SCI-R
- PSS

**Laboratory evaluation:** Glycated hemoglobin, fasting plasma glucose, total cholesterol, HDL-c, LDL-c, triglycerides, serum creatinine, and albumin and creatinine (urine sample)

**Medication use:** Name and daily dosage of medications, vitamins and nutritional supplements, if in use

**Installation of the device:** During installation of the device no data is collected.

**Follow-up phone calls:** General information about well-being and adverse events

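### Section 13 promises to report serious adverse effects but says events will not be classified, and with no hypoglycaemia question or by-arm harms summary, harms cannot be compared reliably between arms

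*Combined protocol and SAP*

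**What the plan says.** **Section 13 (Adverse event monitoring).** The plan expects no adverse events from the intervention. It names stress as a possible effect, and haematoma and local pain from blood collection. It then promises: "Any serious adverse effects beyond these will be recorded and reported". For the follow-up calls it says that "participants will be asked about their well-being and if they have experienced any changes or symptoms since the start of the study". The section closes with "even though specific adverse event classification will not be applicable in this study".

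**Sections 6.3 and 9.1 (calls and data collected).** "Follow-up of participants will be maintained through five follow-up phone calls, conducted every two weeks". In addition, "participants from the control group will receive an extra phone call, equivalent to the device installation". The data listed for the calls are "General information about well-being and adverse events". Table 5 places the last call at week 10. Neither Table 4 nor Figure 1 has an adverse event item at the week 12 visit.

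**Section 6.1 and Tables 1 and 2 (device content).** The device will "automatically issue reminders at specified times for patients to take their medications and insulin", following the attending physician's prescription. Message 19 tells users who check their glucose or "have a hypoglycemia episode, write it down in a notebook". Set 2 of the weekly messages lists the common symptoms of hypoglycaemia.

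**Section 6.2 (control group).** Controls receive a booklet and a QR code to a website that holds the same phrases and podcasts.

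**Section 12 (SAP).** All outcomes are quantitative and analysed by ANCOVA. No summary of adverse events by arm is described.

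**The concern.** A promise to report serious events needs a rule that separates serious from other events. Section 13 gives no such rule and then says that classification does not apply in the study, so staff taking the calls have two instructions that pull apart.

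Hypoglycaemia is the harm most closely tied to what the device does: it prompts prescribed insulin and glucose testing, and it teaches symptom recognition. Section 12.5 makes insulin use a pre-specified subgroup, so insulin users are expected in the sample. Yet the plan has no question, data item or outcome that names hypoglycaemia.

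At stake is the safety counterpart to the HbA1c and self-care results. An excess of reported symptoms in the device arm could reflect more events or better recognition of them, and the plan offers no means of telling these apart. The error could run against the device as easily as for it. Section 17.3 provides for neither a separate data monitoring committee nor formal audits, so section 13 carries most of the safety plan.

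**Working it through.** The documents state no harms figure to reproduce. They give no hypoglycaemia rate, no share of insulin users and no safety sample size. The check is therefore mainly a comparison of passages, with arithmetic to show scale.

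**1. The two statements in section 13.** One requires serious effects to be identified; the other says that classification will not apply. No definition of serious and no reporting timeline appears elsewhere. In Appendix A, SPIRIT item 22, which covers assessing as well as collecting harms, points to p. 20, where section 13 stands. Collection is described there; assessment is not.

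**2. What is asked, and when.**
- Both arms get calls at weeks 2, 4, 6, 8 and 10: 112 × 5 = 560 scheduled calls.
- Controls get a sixth call at week 0. The matching contact in the device arm is the installation visit, at which section 9.1 says no data are collected.
- The question looks back to the start of the study each time. One episode can therefore be reported at up to five calls, and no rule links repeat reports.
- After week 10 no enquiry is listed: 2 of 12 weeks, or 17% of follow-up.

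**3. Is hypoglycaemia captured by name?** It is absent from the outcomes (7.1, 7.2), the data list (9.1), Table 4, the call question (13) and the named anticipated effects (13).

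**4. Exposure to prompts.** By section 6.1's own counts, message 19 is played 3 times and the symptom list 12 times in 12 weeks in the device arm. Controls meet this text only if they open the website. Section 5.3 blinds participants and assessors at baseline only.

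**5. What unequal reporting could do.** With equal true risk, the apparent risk ratio is the reporting fraction in the device arm divided by that in the control arm. The fractions are assumed.

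| Device | Control | Apparent risk ratio | Expected reports per 56 at a true risk of 20% (assumed) |
|---|---|---|---|
| 50% | 50% | 1.00 | 5.6 vs 5.6 |
| 80% | 50% | 1.60 | 9.0 vs 5.6 |
| 90% | 40% | 2.25 | 10.1 vs 4.5 |

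The expected count is 56 × 0.20 × reporting fraction; for example, 56 × 0.20 × 0.80 = 8.96.

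**6. What structured capture could show.** For zero events in n participants, the exact two-sided 95% upper limit is 1 − 0.025^(1/n).
- n = 56 (all randomised to one arm): 6.4%.
- n = 45 (56 × 0.8 = 44.8, the planned 20% dropout): 7.9%.
- n = 28 (if only half an arm were covered, an assumption): 12.3%.

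The one-sided 95% limit for 0/56, 1 − 0.05^(1/56) = 5.2%, is not the figure to quote beside two-sided intervals.

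**7. Power to compare.** With 56 per arm, two-sided alpha 0.05 and assumed control risks of 5%, 10% and 20%, power to detect a doubling is about 17%, 31% and 64%. Any comparison would be descriptive.

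**The case against.** **Harms are collected, and in the same way in both arms.** A reader might infer that the calls gather only well-being, or that harms cannot be compared at all. The documents do not support this. Section 9.1 lists adverse events among the call data, and both arms get the same open question at the same five calls. A crude comparison of reported events is possible; what is missing is a reliable one.

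**The no-classification clause may be narrow.** It follows the sentence about the calls and could mean only that open answers will not be formally coded. Serious effects are promised separately, so it goes too far to say that they could not be counted. This stands as a reading. But the clause refers to the whole study, and serious is undefined under either reading.

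**The device adds no treatment.** Its reminders follow the existing prescription and each patient's own testing routine. Section 12.6 also makes every outcome except the primary hypothesis-generating, without p-values. Both points lower the stakes. Neither supplies a hypoglycaemia count to set beside HbA1c.

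**Bias from the messages is not shown.** Correct. Message 19 plays three times, no figure supports an effect on reporting, and the notebook is not among the data collected. Differential reporting is plausible in an open trial with one-sided prompting; it is not established.

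**Scripted questions would not cure it.** Also correct. Device users would still hear the symptom list weekly, and asking controls about hypoglycaemia is itself a mild prompt, in calls that section 6.3 keeps free of behavioural content. Scripting removes differences in what is asked, but not differences in awareness.

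**Conclusion.** The point holds as a shortcoming worth correcting, not as a failure of the trial. Section 13's two statements must be reconciled, and serious must be defined. Harms, and hypoglycaemia in particular, cannot be compared reliably between arms as planned, for four reasons: the open question does not name hypoglycaemia, it looks back to the start of the study at every call, no enquiry is listed for the last 2 of 12 weeks, and section 12 has no table of harms by arm.

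The size of any distortion is unknown. The apparent risk ratios of 1.6 and 2.25 rest on assumed reporting fractions, and equal reporting would give 1.0. Better capture would allow a bounded statement for each arm (an upper limit of 6.4% for 0/56, or 7.9% for 0/45 after the planned dropout), but not a powered comparison. The primary outcome, its analysis and the sample size are unaffected.

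**What to change.** 1. **Section 13.** Remove the no-classification sentence, or limit it expressly to non-serious symptoms volunteered on the calls. Define serious, and state who applies the definition.
2. **Sections 6.3 and 9.1, Table 4.** At each of the five existing calls and at the week 12 visit, ask both arms the same scripted questions on hypoglycaemia and on serious events, covering the time since the last contact. Record the date of each event, so that repeats can be recognised. Keep the control-only week 0 call out of the comparison.
3. **Section 12.** Add a descriptive table by arm: participants with at least one event and number of events, for serious events and for hypoglycaemia, with exact two-sided 95% intervals for the participant proportions and the denominators stated. Make no hypothesis test, and state that follow-up was unblinded and that only one arm was actively prompted about hypoglycaemia.

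**Cost.** Slightly longer calls, a few REDCap fields and one table. Section 18 says that recruitment began in June 2023, so this is a mid-trial amendment to be reported to the ethics committee and the registry under section 17.4. Participants already enrolled will have unequal capture and should be shown separately; the limits widen accordingly (12.3% for 0/28). Controls receive a mild prompt, which could touch the self-care score, and some open-label reporting bias will remain.

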## 14. Data management and confidentiality

Data will be collected in physical records by the study outcome assessors and stored in a two-level locker room in the research facility. All the data will be entered into a database in the REDCap platform. Outcome variables will be entered in duplicate to ensure data quality. To maintain confidentiality, study participants will be identified using an

identification number (ID), and only the main investigators of the study will have access to identification information (i.e., names) and complete data sets.

## **15. Funding**

This study received funding from the Brazilian National Council for Scientific and Technological Development (CNPq) through the CNPq/MCTI/FNDCT 18/2021 grant. Additionally, the study receives financial support from the Coordination for the Improvement of Higher Education Personnel - Brazil (CAPES), finance code 001. The funders are not involved in the conceptualization, implementation, or analysis of the study. Our research has no affiliation with Amazon, and we do not receive any funding from the company. The Smart Speaker EchoDot 3rd Gen (Amazon Echo®) devices will be acquired with CNPq funding.

## **16. Institutional review board approval**

This study protocol was submitted for approval by the Institutional Review Board (IRB) of Pontifícia Universidade Católica do Rio Grande do Sul. No study procedures were conducted prior to IRB approval.

## **17. Monitoring and additional information**

### **17.1. Composition of the coordinating center and trial steering committee**

The Diabetes and Endocrinology Research Group at the Pontifical Catholic University of Rio Grande do Sul will serve as the coordinating center and trial steering committee for this study.

### **17.2. Trial Sponsor**

The senior investigator of the trial serves as the Sponsor-investigator for this study. They are responsible for ensuring that research ethics principles are followed, supervision, study design, arranging the financing, data collection, statistical analysis, report writing, and the decision to submit for publication.

### **17.3. Frequency and plans for auditing trial conduct**

No formal audits are planned for this study. Instead, the Sponsor-investigator will ensure that the study is implemented in accordance with the protocol and will promptly inform the Research Ethics Committee of Pontifícia Universidade Católica do Rio Grande do Sul of any potential risks that arise during the study. The trial steering committee will

convene at least once a month to assess the progress of the study. Due to the short duration of the trial, the small sample size, and the minimal risk to participants, a separate data monitoring committee was not proposed.

#### 17.4. Communication of important protocol modifications

If necessary, additional protocol modifications will be reported to the Research Ethics Committee of Pontifícia Universidade Católica do Rio Grande do Sul and made publicly available by updating the ClinicalTrials.gov registry by the Sponsor-Investigator. Additionally, any deviations from this study protocol will be reported and justified in all publications related to the study.

#### 17.5. Declaration of interests

The authors declare that they have no competing interests.

### 18. Trial status

This is a protocol (version 3.0, June 2023) for an ongoing trial that started recruitment on June, 2023.

### 19. List of abbreviations

|         |                                                                    |
|---------|--------------------------------------------------------------------|
| SPIRIT  | Standard Protocol Items: Recommendations for Interventional Trials |
| HSL     | Hospital São Lucas                                                 |
| PUCRS   | Pontifícia Universidade Católica do Rio Grande do Sul              |
| SRQ-20  | Self Reporting Questionnaire 20                                    |
| SCI-R   | Self-Care Inventory Revised                                        |
| SF-36   | 36-Item Short Form Health Survey                                   |
| PSS     | Perceived Stress Scale                                             |
| HDL-c   | high-density lipoprotein cholesterol                               |
| LDL-c   | low-density lipoprotein cholesterol                                |
| SAP     | Statistical analysis plan                                          |
| CONSORT | Consolidated Standards of Reporting Trials                         |

|       |                                                                         |
|-------|-------------------------------------------------------------------------|
| BMI   | Body Mass Index                                                         |
| SD    | Standard Deviation                                                      |
| MAR   | Missing at Random                                                       |
| MNAR  | Missing Not at Random                                                   |
| BOCF  | Best Observation Carried Forward                                        |
| ID    | Identification number                                                   |
| CNPq  | Brazilian National Council for Scientific and Technological Development |
| CAPES | Coordination for the Improvement of Higher Education Personnel          |
| IRB   | Institutional review board                                              |

547

548

549

| Section/item                      | Item No | Description                                                                                                                                                                                                                                                                              | Location where item is reported |
|-----------------------------------|---------|------------------------------------------------------------------------------------------------------------------------------------------------------------------------------------------------------------------------------------------------------------------------------------------|---------------------------------|
| Administrative information |         |                                                                                                                                                                                                                                                                                          |                                 |
| Title                             | 1       | Descriptive title identifying the study design, population, interventions, and, if applicable, trial acronym                                                                                                                                                                             | p. 03                           |
| Trial registration                | 2a      | Trial identifier and registry name. If not yet registered, name of intended registry                                                                                                                                                                                                     | p. 03                           |
|                                   | 2b      | All items from the World Health Organization Trial Registration Data Set                                                                                                                                                                                                                 | p. 03                           |
| Protocol version                  | 3       | Date and version identifier                                                                                                                                                                                                                                                              | p. 03                           |
| Funding                           | 4       | Sources and types of financial, material, and other support                                                                                                                                                                                                                              | p. 20                           |
| Roles and responsibilities        | 5a      | Names, affiliations, and roles of protocol contributors                                                                                                                                                                                                                                  | p. 03                           |
|                                   | 5b      | Name and contact information for the trial sponsor                                                                                                                                                                                                                                       | p. 03                           |
|                                   | 5c      | Role of study sponsor and funders, if any, in study design; collection, management, analysis, and interpretation of data; writing of the report; and the decision to submit the report for publication, including whether they will have ultimate authority over any of these activities | p. 21                           |
|                                   | 5d      | Composition, roles, and responsibilities of the coordinating centre, steering committee, endpoint adjudication committee, data management team, and other individuals or groups overseeing the trial, if applicable (see Item 21a for data monitoring committee)                         | p. 21                           |
| Introduction               |         |                                                                                                                                                                                                                                                                                          |                                 |
| Background and rationale          | 6a      | Description of research question and justification for undertaking the trial, including summary of relevant studies (published and unpublished) examining benefits and harms for each intervention                                                                                       | p. 03                           |
|                                   | 6b      | Explanation for choice of comparators                                                                                                                                                                                                                                                    | p. 03                           |
| Objectives                        | 7       | Specific objectives or hypotheses                                                                                                                                                                                                                                                        | p. 03                           |
| Trial design                      | 8       | Description of trial design including type of trial (eg, parallel group, crossover, factorial, single group), allocation ratio, and framework (eg, superiority, equivalence, noninferiority, exploratory)                                                                                | p. 03                           |

| Methods: Participants, interventions, and outcomes           |     |                                                                                                                                                                                                                                                                                                                                                                                |                 |
|---------------------------------------------------------------------|-----|--------------------------------------------------------------------------------------------------------------------------------------------------------------------------------------------------------------------------------------------------------------------------------------------------------------------------------------------------------------------------------|-----------------|
| Study setting                                                       | 9   | Description of study settings (eg, community clinic, academic hospital) and list of countries where data will be collected. Reference to where list of study sites can be obtained                                                                                                                                                                                             | p. 04           |
| Eligibility criteria                                                | 10  | Inclusion and exclusion criteria for participants. If applicable, eligibility criteria for study centres and individuals who will perform the interventions (eg, surgeons, psychotherapists)                                                                                                                                                                                   | p. 04           |
| Interventions                                                       | 11a | Interventions for each group with sufficient detail to allow replication, including how and when they will be administered                                                                                                                                                                                                                                                     | p. 06-11        |
|                                                                     | 11b | Criteria for discontinuing or modifying allocated interventions for a given trial participant (eg, drug dose change in response to harms, participant request, or improving/worsening disease)                                                                                                                                                                                 | p. 06-11        |
|                                                                     | 11c | Strategies to improve adherence to intervention protocols, and any procedures for monitoring adherence (eg, drug tablet return, laboratory tests)                                                                                                                                                                                                                              | p. 20           |
|                                                                     | 11d | Relevant concomitant care and interventions that are permitted or prohibited during the trial                                                                                                                                                                                                                                                                                  | p. 06-11        |
| Outcomes                                                            | 12  | Primary, secondary, and other outcomes, including the specific measurement variable (eg, systolic blood pressure), analysis metric (eg, change from baseline, final value, time to event), method of aggregation (eg, median, proportion), and time point for each outcome. Explanation of the clinical relevance of chosen efficacy and harm outcomes is strongly recommended | p. 12-13, p. 17 |
| Participant timeline                                                | 13  | Time schedule of enrolment, interventions (including any run-ins and washouts), assessments, and visits for participants. A schematic diagram is highly recommended (see Figure)                                                                                                                                                                                               | p. 13-15        |
| Sample size                                                         | 14  | Estimated number of participants needed to achieve study objectives and how it was determined, including clinical and statistical assumptions supporting any sample size calculations                                                                                                                                                                                          | p. 16           |
| Recruitment                                                         | 15  | Strategies for achieving adequate participant enrolment to reach target sample size                                                                                                                                                                                                                                                                                            | p. 04-05        |
| Methods: Assignment of interventions (for controlled trials) |     |                                                                                                                                                                                                                                                                                                                                                                                |                 |
| Allocation:                                                         |     |                                                                                                                                                                                                                                                                                                                                                                                |                 |
| Sequence generation                                                 | 16a | Method of generating the allocation sequence (eg, computer-generated random numbers), and list of any factors for stratification. To reduce predictability of a random sequence, details of any planned restriction (eg, blocking) should be                                                                                                                                   | p. 06           |

|                                                           |     |                                                                                                                                                                                                                                                                                                                                                                                                              |                        |
